Given the lack of research, the primary aim of this study is to elucidate the link between body perception and non-naturalistic auditory information in participants with subthreshold ED symptomatology, as compared to participants without ED symptomatology, using two body illusions. Our primary objective is to investigate the effect of artificial non-naturalistic sounds on the perceived size of a finger in healthy individuals. Previous research has found that this type of sound, which does not contain information on body size, can elicit changes in the perceived size of a finger in a phenomenon known as the 'auditory Pinocchio' illusion [25]. In the first study to report this illusion, it was found that when healthy participants pulled the tip of their right index finger with their left hand and an ascending pitch sound was presented concurrently, the participants both felt and judged their finger to be longer than when the pull was combined with a descending pitch or a constant pitch sound [25]. This illusion builds on the well-known association between changes in pitch and changes in height or size (for a review see [26]). This illusion focuses on a body part (finger) that is not emotionally salient, reducing therefore ‘contamination' by cognitive processes [27]. Nevertheless, given the clinical relevance of studying emotionally salient body parts as they play an essential role in BID [4], and in order to extend the aforementioned research [24], we will adapt the 'auditory Pinocchio’ illusion to a body part that is particularly salient from the emotional point of view for the majority of EDs, namely the waist. We expect that the illusion also occurs for the waist (horizontal position) as for the finger (vertical position) since besides the correspondence with height, pitch is also associated to physical size (at least in the visual domain): static high and low pitches are respectively associated to smaller and larger visual size [28], and ascending and descending pitches are respectively associated to growing and shrinking size [29]. This body of research holds the potential to provide experimental evidence supporting the development of novel therapies, which can target specifically the aforementioned distortions in the perception of sensory body signals, and ultimately BID (e.g., [30]).

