## Aim and hypothesis

### Primary exploratory aim: auditory-driven changes in body perception

The primary aim of this study is to gain an exploratory understanding of the influence on body perception of non-naturalistic auditory information in participants with subthreshold EDs symptomatology using two body illusions. The scarce literature on the topic precludes us from considering a confirmatory model. As a result, the following hypotheses are all descriptive–exploratory.

**Hypotheses 1 (H1)**: Participants with subthreshold ED symptomatology will differ from participants without ED symptomatology in their degree of body image distortion. This hypothesis is exploratory, as alternatively, both groups may show the same degree of distortion.

H1 is based on previous literature that has shown a conflicting set of results. While there is strong evidence to suggest that young females with ED symptomatology and individuals with EDs tend to overestimate their body size compared to control individuals, some evidence suggests that body image distortions are not specific to this population, implying that they can underestimate their body size [24] or even be as accurate as individuals without ED symptomatology [32].

**Hypotheses 2 (H2)**: Participants with subthreshold ED symptomatology will show stronger auditory-driven body illusions, compared to control individuals.

H2 is based on the traditional hypothesis in support of a stronger influence of external sensory signals, leading to stronger body illusions in people with and subthreshold EDs [15–17].

**Hypotheses 3 (H3)**: Participants with subthreshold ED symptomatology, as compared to without ED symptomatology, will present unusual patterns of results in the finger elongation or shrinking waist illusion, suggesting impairments in the integration of artificial auditory signals into their body image.

H3 hypothesizes that participants with subthreshold ED symptomatology, as compared to people without ED symptomatology, will present unusual patterns of results, that is, the perceived finger elongation or shrinking waist will not necessarily occur in the ascending pitch condition (or not only in that condition, as in [24]. The results will shed light on whether the alteration in the mechanisms integrating auditory signals into body image is present only to natural signals related to body weight/size (e.g., footsteps) or it is linked to any auditory signals.

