**Hypotheses 4 (H4)**: Participants with subthreshold ED symptomatology, as compared to people without ED symptomatology, will experience the finger illusion but not the waist illusion, suggesting that the experience of the illusion is linked to the emotional salience of the body part rather than the nature of the auditory signals.

H4 hypothesizes that participants with subthreshold EDs symptomatology will experience the illusion for the finger (not emotionally salient body part), replicating previous research (see [25]) but not for the waist (emotionally salient body part). In that case, the experience of the illusion will not be linked to the nature of the auditory signals (natural sound vs. artificial sound), but to the emotional salience of the body part (finger vs. waist).

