### Statistical analyses

#### Primary aim: auditory-driven changes in body perception Baseline measures

To determine differences between the groups, analyses will be performed with a Student's t-test paired comparison (for normal distribution) or Wilcoxon tests (for non-normal distribution) for ED symptomatology (EDE-Q), interoceptive body awareness (MAIA), sensory-processing sensitivity (HSPS) and body size discrepancy (Body visualizer tool).

#### Experiment 1 and Experiment 2

For the estimations of body part position/size, confidence task and items from the body feelings questionnaires we will follow a 2 × 3 ANOVA within-between interaction repeated-measures design (see Table 2). Specifically, we will use non-parametric ANOVAs on aligned rank (ART) data, suitable for ordinal data, using the R package ARTool [56]. The ANOVAs will involve a group factor with 2 levels (subthreshold EDs and controls) and a feedback condition factor with 3 levels (‘ascendent’, ‘constant’, ‘descendent’). Prior the analysis, assumptions of independence, normality and sphericity will be checked. As in [24], we will include the degree of body size discrepancy as covariate in case of significant baseline differences. Appropriate post-hoc tests will be conducted in case of significant differences.

**Table 2 Tab2:** ANOVA 2 × 3 design

Group	Feedback condition		
	Ascendent	Constant	Descendent
Subthreshold EDs	Subthreshold EDs–Ascendent	Subthreshold EDs–Constant	Subthreshold EDs–Descendent
Controls	Controls–Ascendent	Controls–Constant	Controls–Descendent

For body size discrepancy, we will follow a 2 × 3 ANOVA within-between interaction repeated-measures design (see Table 3). The ANOVAs will involve a group factor with 2 levels (subthreshold EDs and controls), a time factor with two levels (baseline and post-experiment) and a feedback condition factor with 3 levels (‘ascendent’, ‘constant’, ‘descendent’).

**Table 3 Tab3:** ANOVA 2 × 2 × 3 design

Group	Baseline	Experiment		
		Feedback condition		
		Ascendent	Constant	Descendent
Subthreshold EDs	Subthreshold EDs Baseline	Subthreshold EDs Post-experiment Ascendent	Subthreshold EDs Post-experiment Constant	Subthreshold EDs Post-experiment Descendent
Controls	Controls Baseline	Controls Post-experiment Ascendent	Controls Post-experiment Constant	Controls Post-experiment Descendent

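### H4 draws a finger-versus-waist conclusion that no planned analysis tests, and the expected waist direction differs between the Background and H3

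*Protocol article*

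**What the plan says.** **Hypotheses (Aim and hypothesis).** H2 expects that the subthreshold group "will show stronger auditory-driven body illusions, compared to control individuals". H3 expects an unusual pattern relative to women without symptoms, in that "the perceived finger elongation or shrinking waist will not necessarily occur in the ascending pitch condition". H4 expects that the group "will experience the finger illusion but not the waist illusion, suggesting that the experience of the illusion is linked to the emotional salience", and in that case sets aside the type of sound as the explanation.

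**Analyses (Statistical analyses).** For position and size estimates, confidence ratings and questionnaire items: "The ANOVAs will involve a group factor with 2 levels (subthreshold EDs and controls) and a feedback condition factor with 3 levels". Table 2 shows the same two factors. The model in Table 3 adds time and applies only to the body visualizer. The remaining analyses are correlations with EDE-Q score and regressions run for each experiment.

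**Expected direction (Background).** For the finger, with an ascending pitch "the participants both felt and judged their finger to be longer than when the pull was combined with a descending pitch" or a constant one. The illusion is expected to occur for the waist as well, because pitch is also tied to size. Two correspondences are cited. For steady tones it says: "static high and low pitches are respectively associated to smaller and larger visual size". For tones that change, the article instead says: "ascending and descending pitches are respectively associated to growing and shrinking size".

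**The concern.** H4 carries the study's main interpretive contrast: does the emotional salience of a body part, rather than the kind of sound, explain an altered illusion? Answering that needs finger and waist to be compared. With a separate group by feedback model for each experiment, the only available reading is that one result crossed the significance line and the other did not. Two equal effects can easily fall on opposite sides of that line, and a non-significant waist result does not show that the waist illusion is missing.

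The waist has a second problem. If its expected direction is not fixed beforehand, the same observed group difference can be assigned to different hypotheses after the data are seen.

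**Working it through.** **1. Is there a finger–waist comparison anywhere?**
- Estimates, confidence and questionnaire items: group (2) × feedback (3). No body part.
- Body visualizer: group × time × feedback. No finger measure.
- EDE-Q correlations: whole sample, no contrast between body parts.
- Regressions: one set per experiment.
- Post-hoc tests: they follow the models above, so they stay within an experiment.

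The data would allow the comparison. The General experimental procedure has the same women complete both experiments, and actual finger length and waist width are measured.

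**2. How often would discordant significance arise by chance?** The article gives no power or sample size calculation to reproduce.

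- From the article: 50 per group, alpha 0.05 (taken as two-sided).
- Assumed: a one-sample t test on each woman's illusion score (ascending minus descending) as a stand-in for the planned aligned-rank test; standardised effect dz of 0.2 to 0.6, equal for finger and waist; finger–waist correlation r of 0 to 0.5.

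Power p comes from the noncentral t with 49 df and noncentrality dz × √50 (for dz = 0.4, 0.4 × 7.07 = 2.83). With independent tests, P(finger significant, waist not) = p(1 − p):

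| dz | p | p(1 − p) |
|---|---|---|
| 0.2 | 0.284 | 0.203 |
| 0.3 | 0.548 | 0.248 |
| 0.4 | 0.792 | 0.165 |
| 0.5 | 0.934 | 0.062 |
| 0.6 | 0.986 | 0.014 |

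The same women provide both scores, so correlation matters. Simulation with 20,000 studies per cell gave:

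| dz | r = 0 | r = 0.3 | r = 0.5 |
|---|---|---|---|
| 0.3 | 0.241 | 0.207 | 0.169 |
| 0.4 | 0.161 | 0.137 | 0.118 |
| 0.5 | 0.061 | 0.053 | 0.047 |

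A direct paired finger-minus-waist test in the same simulations rejected in 4.8% to 5.4% of studies.

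H4 is stated relative to controls. If controls must also show a significant waist illusion, with the same dz and n, the figures are multiplied by p because the groups are independent:
- dz 0.4: 0.118 × 0.792 = 0.09 to 0.165 × 0.792 = 0.13
- dz 0.3: 0.169 × 0.548 = 0.09 to 0.248 × 0.548 = 0.14

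**3. What could the direct contrast detect?** Suppose the waist illusion is smaller by L (in SDs of the illusion score) in the subthreshold group only. The finger-minus-waist score has SD √(2 − 2r), which is 1.414, 1.183 and 1.000 at r = 0, 0.3 and 0.5. The between-group effect is L/√(2 − 2r). Two-sample t power with 50 per group:
- L = 0.4: effects 0.28, 0.34 and 0.40; power 0.29, 0.39 and 0.51
- L = 0.6: effects 0.42, 0.51 and 0.60; power 0.56, 0.71 and 0.84

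**4. Waist direction, side by side.** The stimuli are sweeps (ascending 700 to 1200 Hz, descending 700 to 200 Hz). The Background's statement about changing pitch makes ascending go with growth; its statement about static pitch runs the other way. H3 takes shrinking under the ascending tone as the usual waist pattern. Now suppose the subthreshold waist widens under the ascending tone and the control waist does not:
- with the changing-pitch sign, this is a stronger illusion (H2);
- with H3's sign, it is an unusual pattern (H3);
- also with H3's sign, the shrinking illusion is absent (H4).

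**The case against.** **The study is exploratory.** The article says all hypotheses are descriptive and exploratory, makes the salience reading conditional, concedes that power may be insufficient for each hypothesis and urges caution. This lowers the stakes. It does not supply the missing comparison, because H4 still attaches a specific mechanism to a pattern that no model tests. Nor is this simply a detail left to an analysis plan, since the article itself fixes the factors of the model.

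**A reader might infer that H2, H3 and H4 cannot be told apart at all, or that any waist result fits both H2 and H3.** The article does not support that. The finger direction is fixed (ascending means longer), so the sign of the contrasts separates H2 from H3 there. H2 to H4 are also all stated relative to women without symptoms. If both groups show the same waist pattern, in either direction, neither H2 nor H3 is supported, and the planned group by feedback interaction can show a departure from controls whatever its sign. The ambiguity arises only when the groups differ at the waist.

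**The waist direction may not be a flat contradiction.** The Background's expectation for the waist concerns whether the illusion occurs and gives no explicit sign, and the static-pitch correspondence in the same sentence points towards smaller size. That may be where H3's shrinking comes from. But the correspondence given for changing pitch points to growth, so the two sections still need reconciling.

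**The chance figures depend on assumptions.** This stands: 25% is the ceiling of p(1 − p), correlation and a control requirement both lower the figure, and at dz 0.6 with independent tests it is only about 1%.

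**Conclusion.** The concern holds in two limited parts.

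First, no planned analysis compares finger with waist, so H4 would be read from discordant significance. If the true illusions are equal, this yields the H4 pattern within the subthreshold group in about 12–16% of studies at dz 0.4 and 17–25% at dz 0.3. Adding a required control waist illusion brings these to roughly 9–13% and 9–14%. The figures rest on the assumed effect sizes, correlations and t test; the absence of the contrast rests on the text alone.

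Second, the Background and H3 differ on what an ascending tone should do to the waist. That leaves a widening open to three hypotheses when the groups differ there. The finger is unaffected.

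Neither part undermines the whole plan, but both should be corrected before analysis.

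**What to change.** - Add a group × body part × feedback analysis of finger length and waist width, each scaled to the woman's measured size. A focused alternative with one degree of freedom takes each woman's illusion score (ascending minus descending, signed in the expected direction for that body part), forms the paired finger-minus-waist difference and compares it between groups. This drops the constant condition, so it answers a narrower question than the three-level interaction.
- Base H4 on that contrast with its confidence interval, not on a null waist test.
- Include experiment order only if it varies. The text does not say that it does, and the Fig. 2 image is not available.
- Reconcile the Background with H3 by stating one signed expected waist direction before analysis. Define H3's unusual pattern as a group difference from controls in that signed score.

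**Cost.** One further analysis of data already being collected and some rewording. Two limits should be stated. With 50 per group, power for a 0.4 SD loss is only about 29–51% under the assumed correlations. The tasks also differ in method: finger length is the difference of two clip settings, whereas waist width averages an opening and a closing setting. A body-part difference would therefore not by itself prove salience.

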S-EDE-Q†	To assess body EDs psychopathology. Self-administered questionnaire composed of 28 items using 7-point Likert scales ranging from 0 (not at all) to 6 points (markedly) about the previous 28 days. Four subscales are measured, including: dietary restraint (5 items), shape concerns (8 items), weight concerns (5 items), and eating concerns (5 items). For each subscale, the score ranges from 0 and 6 points. Participants will be grouped according to a global index score which is the average of the four subscale scores. As in Mond et al. [36], we will use a cut-off point ≥ 2.8 as clinically significant. Higher scores indicating a higher ED pathology. The S-EDE-Q have shown adequate internal consistency (Cronbach’s alpha ≥ .81 for all subscales), acceptable sensitivity (≥ 0.95), specificity (≥ 0.90), and positive (≥ 0.59) and negative (≥ 0.99) predictive values, and positive and significant correlation (≥ 0.70) with EDE diagnoses	X		
HSPS‡	To assess the tendency to process stimuli and information more strongly and deeply than others (sensory-processing sensitivity). Self-administered questionnaire composed of 27 items using 7-point Likert scales ranging from 0 (not at all) to 6 points (markedly). Five subscales are measured including: (1) sensitivity to overstimulation (9 items); (2) aesthetic sensitivity (6 items); (3) low sensory threshold (5 items); (4) fine psychological discrimination (4 items); (5) harm avoidance (3 items). For each subscale, the score ranges from 27 to 189 points. Higher scores indicate higher sensitivity level. A total global score will be obtained by averaging the five subscales. The HSPS have shown adequate internal consistency (Cronbach’s alpha ≥ 0.81 for all subscales) and construct validity in the adult Spanish population	X		

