**Fig. 3 Fig3:**
[figure not shown]
Experiment 2 experimental setup. (**a**) The participants will sit in front of a table, with both hands pressed and pulled out against their waist. A black cloak will be tied around the participant's neck; the other side of the cloak will be attached to the bottom of the table to prevent the participant seeing their body. (**b**) Similarly to Experiment 1, to detect the task of pressing and pulling out the participant's waist and activate the auditory stimulation, a force-sensitive resistor will be placed on one finger. The FSR will interface to a computer through an Arduino microcontroller. Likewise, Presentation® software version 18.0 will be used for stimulus delivery and response recording. (**c**) A horizontal ruler will be used to collect the participants' estimates of their waist width. The ruler will be located on the table. The ruler will be dark on the side facing the participant. Two horizontal metal clips will be mounted on the ruler, each with a red dot that will serve as visual points that the participant will use to mark their waist position. A red fixation point will be placed on the middle of the table

Prior to the experiments, participants will be asked to remove any jewellery from their hands and verbal and written instructions about the tasks will be given to them. Before each experiment, anthropometric data (in centimetres, thereafter ‘cm’) will be collected (finger length and waist width). Next, participants will be accommodated in the experimental setup and equipped with the pressure sensor (fixed with rubber bands) and the headphones. First, participants will be asked to complete the “anchor” task, which consists of pressing and pulling their right index fingertip with their left hand (in Experiment 1) or pressing and pulling out their waist with their index fingertips (in Experiment 2) twenty times, an action that triggers the ‘anchoring’ tone on each occasion (as in [25]). Note that during this task, participants will not be exposed to the ‘ascending’ or ‘descending’ tones. The “anchor” task uses a standard tone to facilitate participants pair the motor action and the production of a sound [25]. Having completed the “anchor” task, participants will be asked to complete a practice task, one trial for each feedback condition. Later, participants will be asked to complete the experimental block.

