#### Experiment 1 procedure: Finger

First, the length of the index finger of the participant’s right hand will be measured by the experimenter using a vernier calliper from the proximal crease at the base of the finger to the tip of the finger. Next, participants will be required to complete an "anchor" task. In this task, participants will be asked to press and pull out their right index fingertip with their left hand twenty times, an action that will trigger the ‘anchoring’ tone on each occasion. After completing the anchor task, participants will complete a practice task, one trial for each feedback condition.

In each practice trial, participants are required to stare straight at the red fixation point and complete the simple action of pressing and pulling their right index fingertip with their left hand while keeping the right index finger in a fixed position (straight against the plastic panel and metal bar, see Fig. 1). One of the three experimental tones ('ascending,' 'descending,' or 'constant') is triggered by the pressing/pulling action. Participants are instructed to continue pressing and pulling their fingers until the sound is no longer audible and, once the sound stops, to relax their left hand while continuing to grasp their right finger with the left hand. They will be then asked to estimate the position of their right fingertip and knuckle by having the experimenter adjust the two visible points on the ruler clips. This adjustment will be done as follows: First, the experimenter will move the top clip downwards at a continuous speed until the participant indicates that the visual point on the clip has reached the fingertip position with a "*Stop*" signal. Following a similar procedure, the experimenter will move the bottom clip upwards at a continuous speed until the participant indicates that the visual point on the clip has reached the knuckle position with a "*Stop*" signal.

Additionally, for each estimation (fingertip and knuckle), the feeling of confidence with the estimations made will be assessed.

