In each practice trial, participants are required to look straight at the red fixation point in the middle of the table and complete the simple action of pressing and pulling their waist with both hands while keeping them fixed to their waist (see Fig. 2. One of the three experimental tones ('ascending,' 'descending,' or 'constant') is triggered by the pressing and pulling action. Participants are instructed to continue pressing and pulling their hands until the sound is no longer audible and, once the sound stops, to relax both hands (while keeping touching their waist). They will then be asked to determine the width of their waist by having the experimenter adjust the two visible points on the ruler clips. As a paradigmatic example, this adjustment will be done as follows: as in Keizer et al. [18], first, the experimenter will move both clips closer together at a continuous speed until the participant indicates that the clips have reached the perceived waist width position with a "Stop" signal. Similarly, the starting point of the aperture width (A) will be set at A = 2.0 × W (W = waist width in cm). This will be repeated while the clips are closed, and while the experimenter pressed and pulled them apart. The initial position of the clips will be counterbalanced across the trials. For both conditions we will collect waist width estimation measurements. Similarly, for each condition, the feeling of confidence with the estimation will be assessed and an average score will be obtained.

As in the finger experiment, the experimenter will use the measurements on the back of the ruler to record the position of the clips, rounding to the nearest 0.5 cm. After completing the practice task, the experimental block will begin. They will repeat the task for thirty trials. Each experimental tone will be presented ten times. The order of the trials will be randomized among participants. Participants will have an opportunity to rest after each 10 trials.

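### H4 reads a finger-yes, waist-no pattern as an effect of emotional salience, but the two tasks differ in more than salience and the planned ANOVAs do not compare them

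*Protocol article*

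**What the plan says.** H4, under the primary exploratory aim of the Protocol article, compares the subthreshold group with women without symptoms. It expects the first group to show the illusion for the finger but not for the waist, "suggesting that the experience of the illusion is linked to the emotional salience of the body part". The explanatory text below it no longer mentions the controls. It says that the illusion would then be tied not to the kind of sound "but to the emotional salience of the body part (finger vs. waist"). All the hypotheses carry a general qualifier: "the following hypotheses are all descriptive–exploratory".

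The two tasks are described as follows.

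- **Axis.** Background: "We expect that the illusion also occurs for the waist (horizontal position) as for the finger (vertical position").
- **Action.** General experimental procedure: the right index fingertip is pulled with the left hand ("in Experiment 1) or pressing and pulling out their waist with their index fingertips (in Experiment 2").
- **Read-out, finger.** Experiment 1 procedure: "the experimenter will move the top clip downwards at a continuous speed", and the bottom clip then moves up. Data management forms finger length as fingertip minus knuckle.
- **Read-out, waist.** Experiment 2 procedure: "the experimenter will move both clips closer together at a continuous speed", and the run is repeated from closed clips. Data management averages the two responses.

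Background and Participants take the salience of the waist, and its absence for the finger, from the literature or by assertion. The Statistical analyses section gives each outcome a group by feedback ANOVA, and body part is not a factor. It also plans a whole-sample correlation between the position and size estimates and EDE-Q scores.

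**The concern.** H4 equates finger versus waist with low versus high salience. Everything else that distinguishes the two tasks moves with body part, so an absent waist illusion has several possible causes. Because the two experiments are analysed separately, the H4 pattern would in practice be read from a significant result in one and a non-significant result in the other. That is not a test of a difference.

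Salience is the clinical message of H4. The Sample size section says that meaningful results are to found a larger confirmatory study, so a mechanism assigned wrongly here would be carried into that study.

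**Working it through.** The plan states no figure on this point, so there is none to reproduce. The check has four parts.

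**1. The tasks side by side**

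| Feature | Finger | Waist | Can it change the effect of tone? |
|---|---|---|---|
| Axis and pitch mapping (Background) | Vertical; illusion reported before | Horizontal; an adaptation resting on pitch-size links, supported at least for vision | Yes |
| Action (General procedure; Experiments 1 and 2) | One fingertip pulled by the other hand | Both sides pressed and pulled | Yes |
| Read-out (Data management) | Difference of two landmarks | Mean of closing and opening runs | Mainly noise |
| Clip start (Fig. 1; Experiment 2) | 10 and 50 cm for everyone | Closing run from 2.0 × waist width; opening run from closed | Mainly noise |

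The waist mapping is not settled within the article. Background links ascending pitch with growing size, while H3 associates the ascending tone with a shrinking waist. A weak or conflicting mapping could produce a null waist result with no part played by salience.

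**2. What the different tests would show**

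This is an illustrative simulation of 4,000 runs with 50 women per group. The outcome is each woman's ascending-minus-constant contrast for finger and waist. The effects (0 to 0.5 SD), the finger-waist correlation (0.3) and the noise ratios (1 and 2) are assumptions, not protocol figures. All tests are two-sided at 5%.

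| Scenario | Subthreshold: finger significant, waist not | Subthreshold: direct finger vs waist | Group × body part |
|---|---|---|---|
| Equal effects (0.5), equal noise | 5% | 6% | 5% |
| Waist twice as noisy, both groups | 53% | 5% | 5% |
| Waist task weaker in both groups (0.5 vs 0.1) | 83% | 63% | 5% |
| Subthreshold group loses the waist effect (0.5 to 0), cause not salience | 89% | 82% | 53% |
| Same means, cause is salience | 88% | 83% | 55% |

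Two hand checks agree:

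- *Row 2, first column.* Finger: 0.5 × √50 = 3.54, power about Φ(3.54 − 2.01) = 0.94. Waist: 0.25 × √50 = 1.77, power about Φ(1.77 − 2.01) = 0.41. Under independence, 0.94 × 0.59 = 0.55; the positive correlation lowers it slightly.
- *Rows 4 and 5, last column.* SD of finger minus waist = √(1 + 1 − 2 × 0.3) = 1.18. Standard error of the group difference = 1.18 × √(2/50) = 0.237. 0.5/0.237 = 2.11, and Φ(2.11 − 1.98) = 0.55.

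Rows 4 and 5 agree by construction. The two causes imply the same means, so no test on these outcomes can separate them.

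**3. Read-out noise**

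Let a single judgement have independent error SD σ. The finger difference then has SD √2 σ and the waist average σ/√2. With equal σ the finger read-out is the noisier by a factor of 2. Row 2 would need each waist judgement to be about four times as variable as a finger landmark judgement. The article gives no such figures, so the direction of any noise difference is unknown.

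**4. What the EDE-Q can add**

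Table 1 lists "shape concerns (8 items), weight concerns (5 items"), which is 8 + 5 = 13 items. The global score averages four subscales, so these two make up half of the score that defines the groups. One simple correlation at n = 100 is detectable with 80% power at r = tanh(2.80/√97) = 0.28. Showing that a relation is specific to these two subscales is a harder question, and that figure does not cover it.

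**The case against.** The strongest reply is that H4 has a comparator. Both groups do identical tasks, so any effect of axis, action or read-out that is the same in both groups cancels in a group by body-part contrast. The simulation confirms this: the contrast stays at about 5% under a shared task difference. This stands. A reader might infer that the design says nothing about salience, or that the task explains any result equally well; for the group contrast the documents do not support that. What survives is narrower. The planned ANOVAs do not contain the contrast, H4's explanatory text drops the controls, and a group-specific response to touch, proprioception or pitch mapping would not cancel. The Abstract itself says that people with eating disorders may have proprioceptive and tactile impairments.

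Other points on that side also stand in part:

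- Read-out and clip start do not vary with tone. They are weak rivals, acting mainly through noise.
- A reader might conclude that salience is never measured. The body feelings items are in additional files not shown, so only the article's own descriptions can be judged.
- A reader might conclude that shape and weight concern enter only through the global score. The planned correlation names EDE-Q scores without restricting them, so that does not follow.
- The axis difference is disclosed, the hypotheses are exploratory and H4 uses a hedged verb. But the explanatory sentence is flat, and an exploratory label excuses low power, not an attribution that the design cannot separate.
- A fuller analysis plan might add a body-part comparison. The salience attribution would still not follow from it.

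**Conclusion.** The point holds in a limited form. If the subthreshold group shows the finger illusion and not the waist illusion, the plan supports saying that the tasks gave different results and, with the right contrast, that the groups differed in this. It does not support assigning the difference to salience.

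Under the assumed effects, separate tests give the H4 pattern in 53% to 83% of runs from shared task differences alone. A group by body-part contrast brings this back to about 5%, but then gives 53% and 55% for a non-salience and a salience cause of equal size. The percentages depend on the assumed effects, correlation and noise. The conclusion that the two causes cannot be separated does not. Axis with pitch mapping, and action, are the serious rivals; read-out sensitivity is secondary.

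The correction is worth making because the inference is stated in the plan and costs little to restate.

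**What to change.** 1. Restate the H4 conclusion: the illusion differs between the finger and waist tasks, and this difference differs by group. List emotional salience as one candidate explanation beside axis and pitch mapping, action, read-out, and group differences in touch or proprioception.
2. Base it on a direct group by body-part comparison of standardised illusion contrasts, such as ascending minus constant, in place of separate significant and non-significant results. Fix the expected sign for the waist and the common scale beforehand. Percentage of measured finger length or waist width is one option, since both are already measured. Dividing by each task's SD would make a noisier read-out look like a weaker illusion. Report the estimate with its interval.
3. Within the EDE-Q correlations already planned, report the waist contrast and the waist-minus-finger contrast against the shape and weight concern subscales. Treat these as supportive, exploratory evidence and not as a rule for when salience wording is allowed: the subscales describe the person, not the body part.

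The cost is a few sentences, one added contrast on data already collected, and a weaker claim. Power is also modest: about 55% in the simulation even when the subthreshold group loses a 0.5 SD waist effect entirely.
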